#### Data collection

Participating phase I SAMHSA grantees will provide project investigators with a copy of the original grant proposal, progress reports to SAMHSA, minutes of meetings with SAMHSA representatives, and any reports or publications disseminated outside SAMHSA. The hour-long interviews will be conducted with the use of an interview guide and comprised of three parts: (1) a series of semi-structured questions relating to experience with implementing and sustaining the program; (2) a free list exercise [50]; and (3) a template [51] of CFIR domains and components. In particular, we are interested in knowing the following: (1) what, if anything, they wanted to sustain; (2) how they perceive whether it was, in fact, sustained or not; and (3) their ranking of key determinants of sustainment.

All coalition members identified by the site PI, program coordinator, and key informants will be asked to complete a brief web-based survey that includes the full sampling frame of the site coalition thought to engage in the SAMHSA-funded initiative. They will then be asked how long they have known these individuals (in years) and to indicate whether (1) they had worked with each other member in the past year on any issue; (2) worked together in the past year on SAMHSA-funded initiative, program or practice issues; and, if yes, then (3) what types of collaboration each relationship involved (prompting for six areas, including advocacy and policy work, information sharing, program delivery, resource sharing, service delivery, or training/education; and (4) which of the defined members they considered a leader or innovator in the SAMHSA-funded initiative, program, or practice.

#### Data quality and management

All interviews will be digitally recorded and transcribed. Interviewers will then compare transcripts with digital records to insure accuracy of transcription. All field notes, interview transcripts, and interviewer notes summarizing interview and focus group experience will be entered into Dedoose [52]. A data accounting and back-up system will be instituted to keep track of, and facilitate access to, all electronic and hard-copy data.

To insure credibility of findings and enhance the validity and reliability of data collected, all interviews will be reviewed by at least two members of the research team. As described in detail below, consensus on coding and coding procedures and modifications to coding books will occur through regular team meetings. When possible, study results will be presented to informants and other study participants, enabling them to provide comment of results and suggest modifications or additional avenues of investigation. An audit trail of data collected as well as memos and minutes of team meetings, indicating time, place, persons providing information, and persons collecting or analyzing information, will be kept throughout the study.

#### Qualitative data analysis

Three types of qualitative analysis will be used with the data collected during this phase. First, using a methodology of “Coding Consensus, Co-occurrence, and Comparison” developed for prevention research qualitative analysis [53], field notes and interview transcripts will be analyzed in the following manner. Each investigator will review this material and prepare short descriptive statements or “memos” to document initial impressions of topics and themes and their relationships and to define the boundaries of specific codes (i.e., the inclusion and exclusion criteria for assigning a specific code) [54]. Segments of text in field notes and interview transcripts will be assigned codes based on a priori (i.e., from the interview guide) or emergent themes (also known as open coding [55]). Lists of codes developed by each investigator will be matched and integrated into a single codebook. Each text will be independently coded by at least two investigators. Disagreements in assignment or description of codes will be resolved through discussion between investigators and enhanced definition of codes. The final list of codes or codebook will consist of a numbered list of themes, issues, accounts of behaviors, and opinions that relate to program structure, function, development, and sustainment. With the final coding structure, two investigators will separately review transcripts to determine level of agreement in the codes applied. A level of agreement in the codes applied ranging from 66 to 97 % depending on level of coding (general, intermediate, specific) indicates good reliability in qualitative research [56]. Based on these codes, Dedoose will be used to generate a series of categories arranged in a treelike structure connecting text segments grouped into separate categories of codes or “nodes.” These nodes and trees will be used to further the process of axial or pattern coding [55] to examine the association between different a priori and emergent categories. Through the process of constantly comparing these categories with each other, the different categories will be further condensed into broad themes using a format that places program formation, structure, and functioning within the framework of the site’s organizational and system context.

Second, the free lists of characteristics of and requirements for sustainment will be tabulated by counting the number of respondents who mentioned each item and then ordering in terms of frequency of responses. Multidimensional scaling analysis [50] will then be used to identify common and unique characteristics in each of the four SAMHSA-funded programs believed to be associated with sustainment.

Finally, a matrix of sustainment characteristics and requirements will be developed for each of the four SAMHSA-funded programs with a list of the CFIR domains and components on one dimension and the classification of sustainment (e.g., infrastructure, intervention, and outcomes) on the other dimension. Both the organization and content of subgroup matrices will be compared to identify features of coalitions that influence the likelihood of achieving sustainment on each dimension that are specific to particular SAMHSA programs and features common to all four programs [51]. Comparison of these matrices will also enable project investigators to compare the project director, coordinator, and coalition member perspectives elicited during extended semi-structured interviews. The project investigators will then select a set of common and specific elements to be incorporated into the design of a heuristic model of sustainment.

#### Social network analysis

The matrix of ties used to analyze advice networks will be constructed from data collected from the web-based survey, supplemented by data collected during the qualitative interviews [57]. The social network analysis will proceed in three stages: network visualization, structural analysis, and statistical analysis of outcomes. The network visualization will be accomplished using NetDraw 2.090. The spring embedder routine will be used to generate the network visualizations [58]. Structural analyses will then be conducted on these network data using Ucinet for Windows, Version 6 [59]. Several network level measures of structure will be assessed, including total number of ties, network size, density (the number of reported links divided by the maximum number of possible links), average distance between nodes, and the number of components (i.e., unique sub-networks). To assess status and interconnectivity within the network, we will calculate degree centrality for incoming ties (being nominated by alters) and outgoing ties (nominating alters). In-degree and out-degree centrality scores assess the relative status of a given node. We will also examine several other measures of network status, including between-ness, closeness, and eigenvector centrality. Eigenvector centrality also allows one to examine in- relative to out-ties, but in- and out-degree centrality correspond directly to counts of nominations by and toward an actor, and as such have a straight-forward substantive interpretation, which eigenvectors lack. Homophily (i.e., likeness between individuals in a network based on specified criteria) data will be assessed on two key variables of interest, the SAMHSA program funding the grantee and sustainment (sustained, not-sustained). Homophily scores can be regarded as the proportion of individuals in a person’s network who share a characteristic with that individual.

### Phase 2

During this phase, we will identify data already being collected by SAMHSA corresponding to the relevant CFIR domains and components identified in phase 1. These data will be found in the Transformation Accountability (TRAC) data collection system for the GLS and PPS grantees, the Coalition Online Management and Evaluation Tool (COMET) for the STOP Act grantees, and the Performance Management Reporting Tool (PMRT) for the SPF-SIG grantees. This identification will include sustainment components that are collected across all four programs and components that are unique to each program.

Second, we will identify data relevant to sustainment not routinely collected by SAMHSA. This will be accomplished by comparing the matrix for relevant data elements identified in phase 1 with the list of common and unique sustainment data elements identified in the first activity of phase 2.

Third, we will design the Sustainment Measurement System (SMS), which integrates data currently being collected as part of existing SAMHSA data collection and reporting systems, and data that can be used to assess progress toward and likelihood of sustainment of project infrastructure, process (i.e., interventions and activities supported by the infrastructure), and outcomes. The SMS will be similar to the Stages of Implementation Completion (SIC) measure described above but involve ordinal scales with three or four categories so that sophisticated Item Response Theory (IRT) analyses can be conducted (see “Data analysis” section below). Like the SIC, it will also have separate sections pertaining to different roles in implementation, e.g., grantee administration, community coalition, and program home-site coordinator. In this instance, the tool will consist of all the elements identified in phase 1 as being relevant (i.e., a potential predictor or requirement) to sustainment of project infrastructure, process, and outcomes. The tool will also include the respondent’s assessment of whether or not sustainment has been achieved with respect to each of these categories, weighted on the basis of priority assigned by respondent to each category. Respondents will be asked to indicate what sustainment components are present and when key benchmarks of process were achieved.

A prototype measurement system will be developed that includes (1) data requesting (e.g., by whom, when); (2) data integration (e.g., with SAMHSA and additional data); (3) analytics (e.g., index to predict sustainment); and (4) visualization (e.g., profile to identify strengths and weaknesses). This will be developed in collaboration with SAMHSA as well as grantees to ensure utility and usability.

### Phase 3

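### The tie matrix is called an advice network and both degree scores are read as status, but the survey asks nothing about advice and only in-degree on the leader/innovator item can carry status.

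*Protocol article*

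**What the plan says.** In the Protocol article, Phase 1, Social network analysis, the plan states: "The matrix of ties used to analyze advice networks will be constructed from data collected from the web-based survey". It adds that these data are "supplemented by data collected during the qualitative interviews". Degree centrality is then computed for incoming and outgoing nominations, with the stated purpose of assessing status and interconnectivity. The interpretation given is: "In-degree and out-degree centrality scores assess the relative status of a given node". The same paragraph says that eigenvector centrality also lets one look at in-ties relative to out-ties.

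Phase 1, Data collection describes the web survey. After a question on how many years the members have known each other, it lists four numbered items:

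- Item 1: whether "they had worked with each other member in the past year on any issue"
- Item 2: whether they "worked together in the past year on SAMHSA-funded initiative, program or practice issues"
- Item 3: the type of collaboration, from six areas: "advocacy and policy work, information sharing, program delivery, resource sharing, service delivery, or training/education"
- Item 4: "which of the defined members they considered a leader or innovator in the SAMHSA-funded initiative, program, or practice"

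The text does not say which item or items supply the matrix used for each network measure.

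**The concern.** The analysis section names a construct (advice) and an interpretation (status from both degree scores). The data collection section describes an instrument that does not measure the first and supports the second only in part. The article both lists the items and names the network, so this is a disagreement between two statements and not simply detail left to a fuller document.

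Two things are at stake. First, collaboration ties would be reported as advice ties. Second, a member who names many leaders, or who lists many working partners, would be credited with status on the strength of their own answers. The Conceptual framework section says social networks will receive particular attention, and Phase 3, Data collection carries network information into the survey that feeds the Sustainment Measurement System. A mislabelled construct in Phase 1 could therefore pass into the later measurement work.

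**Working it through.** The plan gives no figure for the network analysis to reproduce. The check sets the survey items beside the measures, followed by a short derivation and an illustrative simulation.

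**Step 1. Items against constructs.**

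| Survey item (Phase 1, Data collection) | Asks about advice? | Direction recorded? | In-degree measures | Out-degree measures |
|---|---|---|---|---|
| 1. Worked together, any issue | No | No, mutual | Connectedness | Connectedness |
| 2. Worked together, funded initiative | No | No, mutual | Connectedness | Connectedness |
| 3. Type of collaboration, six areas | No | No, giver and receiver not asked | Connectedness by type | Connectedness by type |
| 4. Leader/innovator | No | Yes | Status | Number of leaders the respondent names |

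The lead-in on years known is also mutual and does not ask about advice. Four items times two degree measures gives 4 × 2 = 8 pairings. One of them, in-degree on item 4, supports a status reading.

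**Step 2. Can the interviews supply advice ties?** Phase 1, Participants plans interviews with the principal investigator, the coordinator and at least four informants per site, so at least 1 + 1 + 4 = 6 people. The survey goes to all identified coalition members. The three interview topics of particular interest are what was to be sustained, whether it was, and the ranking of determinants. None concerns advice. Interviews could add some ties but are not designed to give a whole advice network.

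**Step 3. Direction on mutual ties.** Let x(i,j) = 1 if i reports a tie with j. In-degree of i is the sum over j of x(j,i), and out-degree is the sum over j of x(i,j). If the tie is mutual and reported completely and accurately, x(i,j) = x(j,i), so the two are equal for every member. In general, in-degree minus out-degree is the sum over j of [x(j,i) − x(i,j)], and only pairs whose two reports differ contribute. On items 1 and 2, and on item 3 as described, any difference is therefore discordant reporting or non-response.

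**Step 4. How much signal remains in degree itself?** In a simulation, each side of a mutual tie reports independently. All inputs are assumptions, not figures from the article: 15 or 30 members, equal or varied member activity, three levels of reporting error and an error-free case, and 1000 replicates each. With error-free reporting, in-degree equalled out-degree throughout. Otherwise:

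| Sensitivity / false-positive rate | R² of in-degree with true number of ties | R² of (in − out) with true number of ties |
|---|---|---|
| 0.9 / 0.03 | 0.75 to 0.94 | 0.03 to 0.07 |
| 0.8 / 0.05 | 0.58 to 0.86 | 0.04 to 0.07 |
| 0.6 / 0.10 | 0.28 to 0.62 | 0.03 to 0.07 |

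For two unrelated variables the expected R² is about 1/(n − 1), which is 1/14 = 0.07 for 15 members and 1/29 = 0.03 for 30. The in-minus-out difference is at chance level. Degree itself is informative about connectedness and weakens as reporting gets worse.

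**Step 5. Eigenvector centrality.** This index scores a node by the scores of the nodes it is tied to. On a directed matrix one version uses incoming ties and another uses outgoing ties. A single score does not compare the two, so the sentence in the article does not describe what the index gives.

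**The case against.** Several points on the other side are sound. Item 4 is a genuine directed nomination, and the analysis section defines incoming ties in nomination language, so in-degree on item 4 is a natural and valid reading that the text does not exclude. Interconnectivity is a stated purpose beside status, and degree on working ties serves it properly. The full survey instrument and interview guide are not shown, and a journal article may leave the mapping of items to matrices to them. Phase 1 is formative work in 10 purposively sampled sites, and no later analysis is tied to a particular degree score. For a directed matrix, incoming and outgoing eigenvector versions exist, so that sentence is loose more than it is consequential.

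A reader might infer that the status scores mainly reflect reporting disagreement. The documents do not support that. The plan defines no in-minus-out contrast for degree, and on mutual ties each degree score mainly measures connectedness unless reporting is poor. A reader might also infer that a non-respondent would be read as having high status. That needs a rule comparing nominations received with nominations given, and the plan states none for degree. A non-respondent simply keeps the in-degree that others report.

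What survives is that the article itself calls the network an advice network and says both degree scores assess status. No listed item supports the first statement. The second is unsupported for out-degree on any item, and for in-degree on items 1 to 3.

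**Conclusion.** The point holds as a mismatch between instrument and analysis. No listed item measures advice, and status can be read from one of eight item-by-measure pairings. Degree on items 1 to 3 is a usable measure of connectedness but not of advice or status, and a difference between in- and out-degree on those items has no substantive meaning.

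This rests on two assumptions: that the article's list of survey items is complete, and that item 3 is asked without direction, as described. Information sharing, resource sharing and training could be directional in substance, and if the instrument asks who gives and who receives, item 3 could be treated as directed. The simulation figures are illustrative and depend on assumed error rates. The conclusion on direction follows from Step 3 and does not depend on them. The correction should be made before the network results are interpreted, but it does not undermine the rest of Phase 1.

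**What to change.** Revise the Social network analysis section as follows.

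1. Build a separate matrix for each survey item and state which measure uses which matrix.
2. Symmetrise items 1 to 3 by a stated rule, and use them for density, distance, components and connectedness. The rule matters. At the assumed sensitivity of 0.8, counting a tie when either side reports it captures 1 − 0.2² = 0.96 of true ties, while requiring both reports captures 0.8² = 0.64.
3. Take status only from in-degree on the leader/innovator item. Do not interpret out-degree as status.
4. Either rename the object of analysis as collaboration and leadership networks, or add one survey question asking from whom the member seeks advice on the initiative.
5. Remove or correct the statement that eigenvector centrality examines in-ties relative to out-ties.

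The cost is rewording and slightly more analysis work, or at most one extra question in a brief web survey. If the survey is already complete, the renaming option needs no new data.

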#### Participants

In collaboration with SAMHSA’s CMHS and CSAP associate directors and senior program staff, we identified two to three grantees within each of the four SAMHSA-funded programs and solicited their participation in the proposed project. These 10 sites include two PPS grantees currently implementing the Good Behavior Game, three SPF-SIG grantees, two STOP Act grantees, and three GLS grantees. These sites were purposefully sampled [49] to reflect diversity with respect to race/ethnicity, geography, quality of evidence supporting funded activities (i.e., the extent to which they are evidence-based or “evidence-informed”) and perceived level of success in achieving sustainment of program activities, infrastructure, or outcomes.

During a 2–3-day visit at each site, investigators will conduct individual semi-structured interviews with the grantee principal investigator, the project coordinator, and a minimum of four key informants representing coalition or community partners purposefully sampled on the basis of the site PI’s assessment of level of engagement in the project (two least engaged and two most engaged). In addition to these detailed interviews, all members of a coalition will also be invited to complete a brief questionnaire containing questions relating to types of interactions among coalition members and their social network relations.

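### Homophily on funding program equals 1 by construction; on sustainment it is either also 1 or needs a member-level answer that the listed survey items do not collect

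*Protocol article*

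**What the plan says.** In the protocol article, the Phase 1 section on social network analysis introduces homophily as "likeness between individuals in a network based on specified criteria" and names two variables for it: "two key variables of interest, the SAMHSA program funding the grantee and sustainment (sustained, not-sustained"). It describes the score as "the proportion of individuals in a person’s network who share a characteristic with that individual". No other attribute is named for homophily.

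The tie matrix is "constructed from data collected from the web-based survey, supplemented by data collected during the qualitative interviews". The Phase 1 data collection section describes that survey as "a brief web-based survey that includes the full sampling frame of the site coalition thought to engage in the SAMHSA-funded initiative". It asks about working relations with the other listed members, how long they have been known, the kinds of collaboration, and who is seen as a leader or innovator. The Phase 1 participants section assigns the sites to programs: "These 10 sites include two PPS grantees currently implementing the Good Behavior Game, three SPF-SIG grantees, two STOP Act grantees, and three GLS grantees".

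The level at which sustainment is coded is not stated where homophily is defined. The aims treat it as a status of a program. The Phase 1 interviews ask respondents for their own view of whether sustainment occurred, and the qualitative analysis compares the views of directors, coordinators and coalition members.

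**The concern.** Homophily is informative only if the characteristic can differ between two people who could be tied. Funding program belongs to the grantee, and the described ties join people attached to the same grantee. The score then reflects how the roster was drawn and says nothing about how people choose their contacts.

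Sustainment has the same problem if it is one status per site. If it is a personal perception, the score is meaningful, but the article describes no source for it among members who are not interviewed.

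The stake is limited but real. These are the only two variables named for homophily, and the project says it will pay particular attention to social networks. A constant cannot show which network features accompany sustainment, and a score of 100% could be misread as a substantive result.

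**Working it through.** The article gives no homophily figure to reproduce, so the check applies its definition to its own data structure.

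**Inputs from the article**
- Score: H_i = s_i / d_i, where d_i is the number of person i's contacts and s_i the number of those who share i's characteristic (social network analysis).
- Network boundary: one site's coalition (Phase 1 data collection).
- Sites: 2 PPS, 3 SPF-SIG, 2 STOP Act, 3 GLS, each under one program (Phase 1 participants).
- Interviewees: the principal investigator, the coordinator and at least four informants, so 1 + 1 + 4 = 6 or more per site (Phase 1 participants).

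**Assumptions, not in the article**
- Each member carries the program of the site whose roster lists them.
- Coalition size is 8 to 40, tie density 0.1 to 0.6, and the share p of members who perceive sustainment 0.5 to 0.9.

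**1. Funding program within a site.** Every contact of i is on the same roster and so has the same program. Hence s_i = d_i, and H_i = d_i / d_i = 1 whenever d_i ≥ 1. With d_i = 0 the score is 0/0, undefined. The variance among scored members is 0.

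**2. Pooling the 10 sites.** The pooled tie matrix has 10 separate blocks with no ties between them, so each H_i stays at 1. With equal coalition sizes, the chance that two randomly chosen people share a program is

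0.2² + 0.3² + 0.2² + 0.3² = 0.04 + 0.09 + 0.04 + 0.09 = 0.26.

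A pooled score of 1 against 0.26 would look like perfect homophily, yet it follows from the roster alone.

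**3. Sustainment coded once per site.** The argument in step 1 applies unchanged: H_i = 1 for every connected member.

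**4. Sustainment coded as each member's perception.** If ties are unrelated to perception, the expected score is p² + (1 − p)²:
- p = 0.5: 0.25 + 0.25 = 0.50
- p = 0.7: 0.49 + 0.09 = 0.58
- p = 0.9: 0.81 + 0.01 = 0.82

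So the score is not fixed at 1. A simulation of 10 closed coalitions over 36 combinations of the assumed values agreed: steps 1 and 3 gave 1 throughout, while perception-based individual scores ran from 0 to 1 in most combinations.

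**5. Who could be scored on perception.** With six interviewees, perception is known for 6/12 = 50%, 6/20 = 30% or 6/40 = 15% of a coalition of 12, 20 or 40. A score also needs each contact's perception. Six people form 6 × 5 / 2 = 15 pairs, out of 66, 190 or 780 possible pairs, which is 23%, 8% or 2%. Four of the six are chosen as the two most and two least engaged, so they do not represent the coalition.

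**The case against.** A reader might infer that both scores must be 1 for everybody. The documents do not support that for sustainment. The homophily text gives no coding level, and the interviews and the comparison of perspectives both record individual views that can differ inside one coalition. The conceptual framework also lists individuals as a level at which elements of sustainment can be measured. That part of the objection stands, and the sustainment conclusion must stay conditional.

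A second objection is that interviews supplement the tie data and that the instruments are not shown, so cross-site ties or a perception item might exist. This cannot be excluded from a condensed article. However, the interview components it describes contain nothing about other sites' coalitions, and the survey questions it lists contain nothing about sustainment.

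A third is that homophily is a small, exploratory part of Phase 1. This is correct. Network size, ties, density, distance, components and the centrality measures are all unaffected, and no sample size or Phase 3 model is stated to rest on homophily.

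Finally, program and sustainment may have been intended as grouping variables for comparing sites. If so, the text needs correcting, because it makes them the criteria for likeness between individuals.

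**Conclusion.** The concern holds for funding program and conditionally for sustainment. Funding-program homophily is 1 for every member with at least one tie, at all 10 sites and after pooling, and carries no information. This rests on ties lying within one site's roster and on one funding program per site, both as the article describes them. Sustainment homophily is also 1 if the variable is a site-level status. If it is a personal perception it can vary, but on the listed items only interviewees could supply it, about 15% to 50% of coalitions of an assumed 40 to 12 members. The defect is confined to this one descriptive measure.

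**What to change.** - Use funding program and site-level sustainment status as grouping variables, and compare density, centrality and homophily between sites across their categories.
- Score homophily on member attributes that vary within a coalition, such as role, sector, or the member's own rating of sustainment.
- State whether sustainment is coded per site or per member. If per member, ask it of all coalition members in the web survey.
- State that members without ties have no homophily score, and report how many there are.

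The cost is a wording change and one or two added items on a survey meant to be brief. Homophily on role or sector answers a somewhat different question from the one now written, so the authors should choose attributes that fit their hypotheses. With 10 sites, two or three per program, the comparisons between sites can only be descriptive.
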